## Methods/design

### Study design and setting

This is a parallel, non-inferiority, randomized controlled clinical trial to compare the effect of crossbow needle therapy and regular acupuncture therapy on KOA patients. The patients will be enrolled among outpatients and inpatients from the acupuncture departments of No. 1 Affiliated Hospital of Guiyang University of Chinese Medicine, No. 2 Affiliated Hospital of Guiyang University of Chinese Medicine, and Chinese Medicine Hospital of Qiandongnan Miao and Dong Autonomous Prefecture. Eligible patients will be randomly assigned to a crossbow needle group and an acupuncture group in a 1:1 ratio. All items from the World Health Organization Trial Registration Data Set are shown in Table 1. The study flowchart is provided in Fig. 1. A Standard Protocol Items: Recommendations for Interventional Trials (SPIRIT) checklist and figure are provided respectively in Additional file 1 and Fig. 2.

**Table 1 Tab1:** All items from the World Health Organization Trial Registration Data Set (SPIRIT checklist, item 2b)

Data category	Information
Primary registry and trial identifying number	http://www.chictr.org.cn; ChiCTR-INR-16008032
Date of registration in primary registry	12 March 2016
Secondary identifying numbers	–
Source(s) of monetary or material support	Special research project of traditional Chinese medicine in 2015 (201507006–01)
Primary sponsor	Institute of Basic Research In Clinical Medicine, China Academy of Chinese Medical Sciences
Secondary sponsor(s)	–
Contact for public queries	[name]; [contact]
Contact for scientific queries	[name], Institute of Basic Research In Clinical Medicine, China Academy of Chinese Medical Sciences, Beijing 100,700, China.
Public title	Miao medicine in knee osteoarthritis study
Scientific title	Crossbow needle therapy of the Miao ethnic minority group on knee osteoarthritis: study protocol for a multicenter, randomized controlled trial
Countries of recruitment	China
Health condition(s) or problem(s) studied	knee osteoarthritis, pain/ankylosis/joint function disturbance
Intervention(s)	Crossbow needle therapy of the Miao ethnic minority group

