### Sample size

The trial is designed to determine the efficacy of crossbow needle therapy on KOA and prove that its clinical efficacy is not inferior to normal acupuncture therapy; therefore, we chose a non-inferiority trial design [21]. Sample size calculation is based on the formula $$ n=2{\left[\frac{\left(\mu \alpha +\mu \beta \right)s}{\delta}\right]}^2 $$, in which μα and μβ are constants and *s* is the combined standard deviation. We set *α* at 0.05 (one-sided), *β* at 0.10, *δ* at 1.5, and *s* at 4.0 (*δ* and *s* based on expert consensus to determine the formula parameters, but not clear as currently), with *μα = μ*_0.05_ = 1.645 and *μβ = μ*_0.10_ = 1.282. After calculation, the sample size of each group should be around 122. Assuming a 20% dropout rate, each group needs at least 153 patients; 306 patients will be recruited in the trial.

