### Randomization and blinding

There are two investigators at each center (referred to as A and B). Investigator A is responsible for entering baseline data of patients and perform randomization, but he will not know the grouping details and will not participate in the treatment. Investigator B is responsible for performing treatment according to the grouping. At each visit, A is responsible for collecting data and entering the data in the electronic data capture (EDC) system. The therapist and the data collector are separate. Statisticians are responsible for data processing and are not aware of the grouping until the end of the trial. Central randomization will be conducted by CLINDA Soft Co., Ltd. (Tianjin, China). A random sequence will be generated with SAS 9.2 (SAS Institute, Inc., Cary, NC, USA) by an independent statistician who is not involved in the study; the sequence will be stored in a central randomization system (interactive web response [IWR] system). Patients will be stratified based on the three different centers and randomly assigned to the crossbow needle group and the acupuncture group in a 1:1 ratio. The crossbow needle group will receive crossbow needle therapy. Regular acupuncture therapy will be performed on the acupuncture group.

In this trial, patients will not be blinded due to the uniqueness of the two therapies. Investigators and statisticians will be blinded. Treatment, data collection, and data analysis will be conducted by trained practitioners, data collectors, and statisticians, respectively, all blinded to one another in order to ensure the reliability of the results.

The conditions for unblinding are: (1) infection or other adverse events (AE)—and these patients will be withdrawn from the trial; or (2) the end of the trial and data analysis.

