### Statistical analysis

Data analysis will be conducted in accordance with the intention-to-treat principle. Missing data will be handled using linear mixed effects models. Statisticians and chief investigators will work out an analysis plan and related forms before database lock. The analysis will include case distribution, comparison of basic values, compliance, effectiveness, factors that influence efficacy, and safety. Statistical analysis will be conducted using SAS 9.2 (SAS Institute Inc., Cary, NC, USA). The Wilcoxon rank sum test, *t* test, or variance analysis will be performed for inter-group or intra-group comparison according to data distribution. The Wilcoxon rank sum test will be used to compare ranked data. The chi-square test will be applied to compare enumeration data. All tests will be one-sided. A *p* value < 0.05 will be considered statistically significant.

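### The listed tests, chosen by data distribution, are tied neither to the non-inferiority margin nor to the mixed model, and an unpaired rank test is listed for within-group use

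*Protocol article*

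**What the plan says.** **Objective and size.** Under Study design and setting: "This is a parallel, non-inferiority, randomized controlled clinical trial". Under Sample size, the authors say of their aim: "therefore, we chose a non-inferiority trial design". The calculation uses the formula for a difference of two means, with one-sided alpha 0.05, beta 0.10, δ = 1.5 and s = 4.0. It concludes that "the sample size of each group should be around 122", raised to 153 for 20% dropout. The values of δ and s are described as "based on expert consensus to determine the formula parameters, but not clear as currently". That section does not say to which outcome scale they belong.

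**Analysis.** The Statistical analysis section states intention-to-treat and then: "Missing data will be handled using linear mixed effects models". It goes on to name the rank-sum test, the t test or "variance analysis will be performed for inter-group or intra-group comparison according to data distribution". All tests are one-sided, with p < 0.05 as the criterion. An analysis plan is to be written before database lock. The section mentions no margin, shifted null hypothesis or confidence limit, and calls no analysis primary.

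**The concern.** The paragraph gives a set of tests and a decision rule, and neither is the one for which the trial was sized. Three things follow.

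- **The question.** A non-inferiority claim needs a confidence limit set against a margin, or a test of a null hypothesis shifted by it. A one-sided p < 0.05 from an ordinary t, ANOVA or rank-sum test answers whether one arm is better than the other.
- **The quantity.** A t test or ANOVA concerns a difference in means; a rank-sum test compares distributions. If the data decide which is used, they also decide what is estimated, and no selection rule is given. The mixed model is named, but the listed tests do not use it.
- **The pairing.** The Wilcoxon rank-sum test is for independent samples. It is the only rank test named, and it is listed for before-after comparison within an arm, where the observations are paired.

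At stake is whether the stated primary comparison can deliver the conclusion that the trial was designed to reach.

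**Working it through.** **1. The plan's own figure.** Inputs from Sample size: z = 1.645 and 1.282, s = 4.0, δ = 1.5, equal arms.

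n = 2 × [(1.645 + 1.282) × 4.0 / 1.5]² = 121.85, so 122 per group. Then 122 / 0.80 = 152.5, so 153 per group and 306 in all. Both figures reproduce.

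**2. What the design delivers if the margin is used.** With true difference 0, power = Φ(δ / [s√(2/n)] − 1.645).

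- n = 122: 1.5 / (4 × √(2/122)) = 2.929; Φ(1.284) = 90.0%.
- n = 153: 1.5 / (4 × √(2/153)) = 3.280; Φ(1.635) = 94.9%.

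**3. What the listed tests deliver if read literally.** With null difference 0 and true difference 0, a one-sided 5% test rejects 5% of the time by construction. Simulation at 122 per arm (SD 4, normal, 20,000 runs) gave 5.1% for both the t test and the rank-sum test. By the formula in step 1, such a test reaches 90% only if crossbow needle therapy is truly better by 1.5, which the plan does not assume.

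**4. Can the tests be set against the margin, and does choosing by distribution do harm?** Each test was shifted by 1.5 at 122 per arm. The plan names no selection rule, so the two-stage choice was assumed to be Shapiro-Wilk at 0.05 in each arm.

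| Data | True difference | t test | Rank-sum | Two-stage |
|---|---|---|---|---|
| Normal (20,000 runs) | 0 (power) | 90.3% | 88.8% | 90.0% |
| Normal (20,000 runs) | 1.5 (error) | 5.0% | 4.9% | 5.1% |
| Exponential (5,000 runs) | 0 (power) | 90.0% | 99.6% | 99.6% |
| Exponential (5,000 runs) | 1.5 (error) | 5.2% | 5.3% | 5.3% |

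The error stays near 5% in every row. The rank-sum results hold under a pure location shift, which is how the data were generated. Without that assumption, a shifted rank-sum test is no longer a test about means.

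**5. Unpaired test on paired data.** With equal variances and within-patient correlation r, the unpaired standard error exceeds the paired one by 1/√(1 − r). By normal approximation, the true size of a nominal one-sided 5% test is 1 − Φ(1.645/√(1 − r)). The documents give no r, so a range is assumed.

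| r (assumed) | SE ratio | True size |
|---|---|---|
| 0.3 | 1.20 | 2.5% |
| 0.5 | 1.41 | 1.0% |
| 0.7 | 1.83 | 0.1% |

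**The case against.** The list of tests is generic. It serves baseline values, compliance, effectiveness and safety together, and it is not called the primary analysis. The one-sided 0.05 matches the alpha of the non-inferiority calculation, so the authors may well intend a shifted test. An analysis plan is promised before database lock, and the statisticians are unaware of grouping until the end of the trial. A selection rule, covariates and the full model can fairly be left to that plan.

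Much of this stands. Blinding and a plan made before lock soften the worry about data-driven choice, and the simulation shows little effect on error. They do not remove the mismatch in what is written: tests and a p-value rule are stated, and the margin is absent from them.

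Two stronger readings are tempting, and the documents do not support them.

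- **That the listed tests cannot be set against 1.5.** A t test or ANOVA yields a mean difference with a confidence limit, and a rank-sum test can be shifted under a location-shift assumption. The plan simply does not say that this will be done.
- **That the plan discards withdrawn patients and so biases the result towards non-inferiority.** Under Combined use of drugs, patients who self-treat for worsening are withdrawn, so losses may depend on outcome. But the plan states intention-to-treat and mixed models for missing data, and the Adherence section provides for follow-up of withdrawals. The fault is that these statements are not joined to the listed tests. Bias from outcome-dependent withdrawal is also not caused by the choice of test: a mixed model assumes missing at random and would not remove it.

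On pairing, the fault is certain only for the rank-sum test. The t test may be meant as paired and the ANOVA as repeated-measures.

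**Conclusion.** The point holds as a mismatch between stated objective and stated analysis. Read literally, the tests would support a claim about 5% of the time when the treatments are equal, against the planned 90%. This rests on taking them as tests of no difference; the section states no null hypothesis, but it offers no other. If the margin is applied to the mean difference, the planned power of 90.0% at 122 per group is recovered, so the design itself is sound on its own inputs.

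Choosing the test by distribution leaves the estimand and the analyst's discretion open. It should not be described as inflating type I error: under the assumed rule, error was 5.1% to 5.3%.

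The rank-sum test is wrong for before-after data. The error is conservative at the assumed correlations and does not touch the between-arm decision.

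**What to change.** Replace the list of tests for the primary outcome with one analysis, used whatever the distribution:

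- **Model.** The linear mixed model already named, on post-baseline WOMAC, with arm, visit, arm-by-visit, baseline WOMAC and centre (the stratification factor).
- **Contrast.** Name one visit as primary, for example end of treatment; the model otherwise gives three arm contrasts.
- **Decision rule.** Higher WOMAC is worse, so conclude non-inferiority if the one-sided 95% upper limit of the crossbow-minus-acupuncture mean difference lies below the margin. State that 1.5 is on the WOMAC scale analysed, and how this relates to the Nimodipine calculation mentioned under Primary outcome measures.
- **Sensitivity.** Keep rank-based results here. Add an analysis that departs from missing at random for patients withdrawn because of worsening.
- **Within groups.** Use a paired t test or the signed-rank test.

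The cost is wording in the Statistical analysis section and the pending analysis plan. The sample size stays at 122, or 153 after dropout. No new data are needed: WOMAC is scheduled at baseline and three later visits, and centre is known from randomisation.

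### One-sided testing at 0.05 is imposed on every comparison, without a direction, although only the primary non-inferiority comparison justifies it

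*Protocol article*

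**What the plan says.** The Statistical analysis section first sets the scope: "The analysis will include case distribution, comparison of basic values, compliance, effectiveness, factors that influence efficacy, and safety". It then names the tests. For continuous data these are the Wilcoxon rank sum test, the t "test, or variance analysis will be performed for inter-group or intra-group comparison according to data distribution". For categories, "The chi-square test will be applied to compare enumeration data". The rule that governs all of them follows: "All tests will be one-sided". The threshold is a p "value < 0.05 will be considered statistically significant".

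The reason for a one-sided level appears elsewhere. The Sample size section says the trial is meant to "prove that its clinical efficacy is not inferior to normal acupuncture therapy"; "therefore, we chose a non-inferiority trial design", with α set at 0.05 one-sided. No other section limits the blanket rule or says which direction any test takes.

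**The concern.** A one-sided test suits a question where only one direction matters. Non-inferiority on the primary outcome is such a question. Baseline balance, compliance, predictors of efficacy, secondary outcomes and safety are not: a difference either way is informative.

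Three things are at stake.

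- A secondary or safety result just below p = 0.05 would rest on weaker evidence than readers normally assume, because the one-sided 0.05 threshold is the two-sided 0.10 threshold.
- A difference in the untested direction could not be called significant however large it was, and the article does not tell the reader which direction that is.
- Some of the named tests have no one-sided form in the settings where they would be used, so the analyst must either break the rule or improvise.

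**Working it through.** **1. The plan's own figure.** Inputs from the Sample size section: α = 0.05 one-sided (1.645), β = 0.10 (1.282), δ = 1.5, s = 4.0, dropout 20%.

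n = 2[(1.645 + 1.282) × 4.0 / 1.5]² = 121.85, so 122 per group. 122 / 0.80 = 152.5, so 153 per group and 306 in total. The stated sizes reproduce, so one-sided 0.05 for the primary comparison is consistent with the design.

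**2. Error of a directional test at 0.05.** The critical value is 1.645 one-sided and 1.960 two-sided. Null simulation with 200,000 draws:

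| Procedure | Error in tested direction | Total type I error (simulated) |
|---|---|---|
| Two-sided 0.05 | 0.025 | 0.050 |
| One-sided 0.05, direction fixed in advance | 0.05 | 0.049 |
| One-sided 0.05, direction taken from the data | not fixed | 0.099 |

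**3. Tests with no direction.** Kellgren-Lawrence grade 1, 2 or 3 (Inclusion criteria) compared between two arms gives a chi-square with (3 − 1)(2 − 1) = 2 degrees of freedom. The three centres (Randomization and blinding) would be a three-level factor if examined as an influence on efficacy. Neither statistic points in a direction. Used as it stands, the 2-df chi-square at p < 0.05 keeps its level (simulated 0.049). If an analyst made it one-sided by halving p, then p/2 < 0.05 means p < 0.10, and the level becomes 0.10 (simulated 0.099).

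**4. Safety.** The Safety monitoring section expects itching, redness and swelling with the crossbow needle, and fainting, stuck needles, hematoma and bleeding with acupuncture. Differences may therefore run either way. The article gives no event rates, so the rates below are assumptions. Normal approximation, n per group, difference d, mean rate p̄:

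power = Φ[(d − z·se₀)/se₁], with se₀ = √(2p̄(1 − p̄)/n) and se₁ = √([p₁(1 − p₁) + p₂(1 − p₂)]/n). For a test aimed the wrong way, d is replaced by −d.

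Example, 5% vs 15%, n = 153: se₀ = 0.0343, se₁ = 0.0338. Two-sided: (0.10 − 1.960 × 0.0343)/0.0338 gives 83%.

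| Assumed rates | n per group | Two-sided 0.05 | One-sided, direction of the true excess | One-sided, opposite direction |
|---|---|---|---|---|
| 5% vs 10% | 153 | 38% | 51% | 0.04% |
| 5% vs 15% | 153 | 83% | 90% | <0.001% |
| 10% vs 20% | 153 | 69% | 79% | 0.002% |
| 5% vs 15% | 122 | 74% | 83% | <0.001% |

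**5. Effect of a correction on size.** Changing sidedness outside the primary comparison does not enter the formula in step 1, so 122, 153 and 306 stand.

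**The case against.** The strongest reply is that a one-sided test with a direction fixed beforehand is a valid 0.05 test. That is right. A reader might infer that the blanket rule doubles the type I error of every test; the article does not support this. Only the error in the tested direction doubles, from 0.025 to 0.05. A total of 0.10 needs a direction chosen from the data or halved p values, and the article announces neither. For multi-category tests the fault is a rule without meaning, not inflation.

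A reader might also infer that harm from the crossbow needle would go undetected. That too goes beyond the text. A one-sided test aimed at excess harm in that arm would have more power than a two-sided one (90% against 83% in the 5% vs 15% example), and every adverse event is to be recorded whatever a p value says. What can be said is that one direction is lost and the article does not say which.

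Nor do the documents support a count of expected false positives over the secondary outcomes. The abstract ties the four assessment times to WOMAC, SF-36 is described as taken before and after treatment, and the schedule figure is not available.

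Two smaller replies also stand. With only two groups, F equals t squared, so the remark on ANOVA applies only to three or more levels. And the article states which way WOMAC, VAS, JOA and SF-36 run, so a direction for those could be set in the analysis plan that is due before database lock.

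None of this rescues the sentence. It is a stated rule, not a detail left open: an analysis plan that followed it would inherit the problem, and one that departed from it would contradict the published protocol.

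**Conclusion.** The point holds in limited form. The blanket rule is unsuitable outside the primary non-inferiority comparison. For directional tests it allows 0.05 rather than 0.025 error in the tested direction and removes any finding in the other. For chi-square tests with more than one degree of freedom and ANOVA with three or more levels it cannot be applied.

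The primary comparison is untouched: its one-sided 0.05 agrees with the sample size calculation. The consequence falls on secondary, influencing-factor and safety statements. The error rates follow from the stated level alone. The safety power figures rest on assumed event rates and only illustrate what is lost when the tested direction is the wrong one.

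**What to change.** Replace the sentence on sidedness with a rule of four parts:

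- one-sided 0.05 for the primary non-inferiority comparison only;
- secondary outcomes, factors that influence efficacy, and safety tested two-sided at 0.05, with two-sided 95% confidence intervals;
- multi-category chi-square tests and ANOVA with three or more levels reported as ordinary omnibus tests;
- baseline characteristics summarised descriptively, since significance tests add little after randomisation.

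Carry the same rule into the analysis plan before database lock. The cost is a short change of text and slightly less favourable secondary p values. Recruitment stays at 306.

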### Safety monitoring

Possible AEs during crossbow needle treatment include itching, redness, and swelling. Fainting, sticking of needle, hematoma, subcutaneous hematoma, and bleeding might occur during acupuncture treatment. Any AE that occurs during the trial will be recorded in a CRF by researchers and patients will be treated as soon as possible. Patients may choose to withdraw from the trial due to any AE. The sponsor and the data management company CLINDA will monitor the implementation of the trial protocol and filling of CRFs.

## Discussion

Crossbow needle therapy is a broad-spectrum therapy mainly used to treat wind syndromes such as cat-head wind (similar to cold Bi syndrome in traditional Chinese medicine), half-wind (similar to stroke), and tendon-wind (similar to sciatica) [11–14]. In terms of modern clinical medicine, it has been applied in the treatment of KOA, cervical spondylosis, and lumbar disc herniation [16, 27, 28].

Crossbow needle therapy has evolved from ancient times when people of the Miao ethnic minority group killed large animals. The poison they spread on arrows was later applied on human after toxicity attenuation. Prescription of the herbal liquid varies from place to place. Its major components include Sheng Cao Wu (*Radix Aconiti Kusnezoffii*), Bai Long Xu (*Disporum bodinieri*) (Levl. et vaut.) Wang et Tang, Hei Gu Teng (*Periploca forrestii*), Tou Gu Xiang (*Gaultheria yunnanensis*), and Da Xue Teng (*Sargentodoxae caulis*) [29], which have sedative, anti-inflammatory, and analgesic effects, and help promote blood circulation and remove blood stasis [30–32].

Ancient crossbow needles were made of sewing needles and bamboo chopsticks or wooden sticks. One or several sewing needles would be stuck into one end of a 15-cm stick, with the needle tip 2 or 3 mm away from the stick (Fig. 4a). Needles would be dipped into the herbal liquid before each needling.

**Fig. 4 Fig4:**
[figure not shown]
Diagram of ancient crossbow needle and skin needle. **a** An ancient crossbow needle. **b** Skin needles

The skin needle is seen as a refined equivalent of the ancient crossbow needle. It is made up of a needle cylinder and a handle, with 30-odd needles embedded in the cylinder. Practitioners usually perform rolling motions along meridians in clinical practice. Compared with the ancient crossbow needle, the skin needle is able to needle more skin area in one application and keep stable contacts with the skin, which reduces painful stimuli. The needle in the cylinder is much thinner than the ancient crossbow needle, decreasing the risk of local hematoma and puncture of internal organs, and easier for young or vulnerable patients to accept skin needle treatment (Fig. 4b) [33, 34].

Administering drugs through the skin is the core of crossbow needle therapy. According to the basic theory of Miao medicine, internal toxins can be driven out of the human body through sweat pores and hair pores on the skin by opening these pores and regulating body temperature. The toxin mentioned here is the source of all diseases in Miao medicine, which believes that all diseases arise from pathogenic toxins. Crossbow needle therapy was developed and intended to open sweat and hair pores by stimulating the skin and administering drugs through the skin into meridians and finally helping drive out internal toxins [35].

According to the basic theory of traditional Chinese medicine, the skin is part of the meridian system and is the external manifestation of the meridian *qi*. On one hand, it is the outermost layer of the human body and plays a defensive role. On the other hand, it connects and affects the inner viscera through the meridian system. When needling is performed, stimuli transmit from the skin through collaterals and meridians to the inner viscera. The process invigorates *Wei qi*, regulates *qi* and blood, balances yin and yang, and finally helps to prevent and treat diseases [36].

From the viewpoint of modern medicine, the skin is the largest organ of the human body and functions to defend the body and regulate immunity. Cuticle layer, pilosebaceous duct, and sweat duct are the three approaches for transdermal drug absorption. The latter two cover only 0.1% of the skin area, so the cuticle layer is the major approach [37]. Nevertheless, the cells in this layer are keratinized dead cells, which can limit the entry of external substances, including drugs. Penetration enhancers enable some small molecule drugs to pass through the skin and reach effective concentrations, but not for most drugs, especially macromolecular drugs [38]. Crossbow needle therapy can solve the problem by puncturing the cuticle layer and passing drugs into the corium layer through the needle puncture holes. This way, drugs can enter the capillary network and reach therapeutic targets at a fast speed with enough concentration, which greatly reduces drug dose and increases drug effect [39, 40]. To date, crossbow needle therapy has been mainly applied on transdermal macromolecular drug delivery [41].

The trial has certain limitations. Drawing knee synovial fluid always leaves a wound, which does not suggest skin needle application should be followed. Therefore, the trial does not include a design to draw knee synovial fluid and conduct further tests. Without these tests, we may lose some objective indexes to evaluate the efficacy of crossbow needle therapy. We will continue to optimize the design in our further study.

